### Intervention group

Participants randomly allocated to the intervention group will participate in an 8-week, twice weekly outpatient supervised exercise training program. The exercise training program will be conducted in an outpatient rehabilitation setting and supervised by an experienced physiotherapy clinician who will closely monitor the participants’ exercise performance and provide appropriate exercise progression. Details of exercise training sites can be obtained at the Clinical Trial Registry ACTRN12616001467426.

The aim is for each participant to complete 20 min each session of cycling and treadmill exercises (40 min in total). Each participant will commence training in the first session by undertaking a minimum of 10 min of cycling and 10 min of treadmill training. Interval training, consisting of 60 s of exercise and 120 s of rest, will be used if participants are unable to complete 10 min of continuous exercise. The duration of cycling and treadmill exercises will be up-titrated such that participants are completing 20 min each session of cycling and treadmill exercises by the end of the second week.

The initial treadmill speed will be set at 60–70% of six-minute walk test (6MWT) speed and titrated up to 90% of 6MWT speed as tolerated over the first 4 weeks of training, by monitoring training heart rate (HR), rating of perceived exertion (RPE) and leg fatigue on the modified Borg scale will be determined. Training intensity will be maintained at this HR and RPE for the remainder of the 8-week training period. An upper limit for exercise intensity will be set at 85% of age-predicted maximum HR and 4 on the 0–10 modified Borg RPE scale. Cycle intensity will be calculated using the 6MWT distance from standard equations [21]. The initial cycle training intensity will be prescribed at 60% of the estimated peak work rate from the 6MWT distance.

Participants will be monitored during training so that their HR is less than 85% of peak 6MWT HR, oxygen saturation (SpO_2_) is above 85%, and RPE is between 3 to 4 on the modified Borg RPE scale. If required, supplemental oxygen will be provided during exercise sessions to maintain SpO_2_ above 85%. Each exercise training session should take approximately 45 to 60 min to complete. Exercise training will be discontinued for participants who suffer any adverse events (including syncope, dizziness or marked worsening in oxygen desaturation during exercise) during exercise training. These participants will be referred to their physician (JF) for assessment and evaluation for suitability to continue the study.

Following the exercise training program, participants will be prescribed a standard home exercise training program. The home exercise program will consist of the participant being asked to walk 3–5 times per week for 20–30 min. Participants will be asked to walk at an RPE similar to which they achieved during the exercise training program. Compliance with the home exercise program will be evaluated at subsequent clinic visits.

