### Control group

The control group participants will continue with their routine medical care and physical activity regimes for the 8-week study period without the additional exercise training intervention. During the 8-week period, participants allocated to the control group will receive a weekly phone call from the study coordinator to review any adverse events and to record exercise habits.

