#### Primary outcome measure

The primary outcome measure will be exercise capacity assessed using the 6MWT at baseline and following the 8-week study period as per the American Thoracic Society and European Respiratory Society guidelines [22].

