Cardiac function will be measured using both cardiac magnetic resonance imaging (CMRI) and echocardiography, with CMRI serving as the principal method. Left and right ventricular end-diastolic volume and end-systolic volume will be measured using CMRI (1.5 T Scanner, MAGNETOM Aera, Siemens Healthcare, Erlangen, Germany) from which stroke volume, ejection fraction, cardiac output and contractile reserve will be derived [28]. In addition, measures of both right and left ventricular mass will be obtained. These will be measured at rest and during 2 submaximal exercise intensities (at 30% and 60% of their respective peak workload determined from incremental exercise test) using the MRI cycle ergometer. During the CMRI, electrocardiogram (ECG) and SpO_2_ will be continuously monitored and the test will be supervised by a medical practitioner. Echocardiographic evaluation will be performed as part of standard clinical protocol on the same day of the 6MWT. This will be assessed both at baseline and following the 8-week study period. Echocardiographic images will be acquired using a 4 MHz matrix array cardiac transducer (Vivid 7, General Electric, Milwaukee, Wisconsin, USA). All images will be attained with the participant in a semi-recumbent position for both the apical and parasternal windows. Right ventricular systolic pressure will be estimated from the tricuspid regurgitation velocity as per standard guidelines [29]. Right ventricular systolic function will also be examined by assessing the tricuspid annular plane systolic excursion.

Adverse responses or events including syncope, dizziness or marked worsening in oxygen desaturation during exercise will be monitored and recorded for the duration of the 8-week exercise training period. Such adverse events will also be assessed with weekly phone calls and recorded for the participants in the control group during the 8-week study period.

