### Data analysis

Individual data will be de-identified, coded and entered into a password protected, secure database. The group allocation for each individual participant will be stored in a separate file at the time of allocation. Data will be double entered and range checks made on values to ensure data integrity. On completion of the study, the primary investigator (PI) will have access to the final trial dataset. An intention-to-treat analysis will be used to avoid bias in estimating the treatment effect for this superiority study, with inclusion of all measures in all available participants, regardless of whether they completed the intervention. We will use a generalised linear mixed model approach which can accommodate missing data points often encountered in longitudinal datasets and provides an ideal way of dealing with missing values or dropouts [33]. Equivalent parametric and non-parametric tests will be conducted where data does not meet normative assumptions. Probability of a Type I error will be set at 0.05. Survival and clinical worsening (event-free survival) will be estimated by the Kaplan-Meier method, using a stratified log-rank test for group comparisons. The commencement of the exercise program or control period will be used as the index date for determining survival or clinical worsening. Participants who have no clinical worsening event will be included up to their first clinic visit after the 2-year period study commencement.

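### The adverse-event rule in the exercise arm merges stopping training with leaving the study, so week-8 outcomes can be lost from one arm only

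*Protocol article*

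**What the plan says.** The Intervention group section gives two instructions in sequence. First, "Exercise training will be discontinued for participants who suffer any adverse events" while training. Second, these participants are referred to their physician "for assessment and evaluation for suitability to continue the study". The first concerns training; the second concerns the study.

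For controls, the Control group section says that they "will receive a weekly phone call from the study coordinator to review any adverse events and to record exercise habits". The Secondary outcome measures section adds: "Such adverse events will also be assessed with weekly phone calls and recorded for the participants in the control group". Neither section attaches a decision about remaining in the study.

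The Data analysis section adopts intention-to-treat, with the stated purpose of avoiding bias in a superiority comparison. It defines who is analysed in these terms: "with inclusion of all measures in all available participants, regardless of whether they completed the intervention". Missing values are left to a "generalised linear mixed model approach which can accommodate missing data points often encountered in longitudinal datasets", which the article goes on to describe as an ideal way to handle dropouts. The primary outcome is "exercise capacity assessed using the 6MWT at baseline and following the 8-week study period".

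**The concern.** Training has already been stopped by the first instruction, so the review that follows reads naturally as a decision on whether the person remains in the trial. Only an event during training triggers it, so only the exercise arm can lose participants by this route. The stated blinding covers outcome assessors, data analysts and the clinical-worsening panel. Nothing says that it covers this decision, and an event during training reveals the allocation.

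A participant taken off study before week 8 has no post-baseline walk test, and may also have no week-8 cardiac imaging or quality-of-life score. If those who tolerate exercise badly are the ones lost, the exercise arm looks better than it is. Week-8 measurements that were never taken cannot be restored by a later analysis plan, so this is a matter of trial conduct and not only of analysis.

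**Working it through.** **1. The passages side by side**

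| Situation | Exercise arm | Control arm |
|---|---|---|
| Adverse event in the 8 weeks | Training stopped; referred for a decision on continuing the study | Reviewed and recorded by weekly phone call |
| Stops training, still measured at week 8 | Kept in the analysis | Not applicable |
| Taken off study before week 8 | Not stated whether measured; if not, no week-8 value | No such step stated |

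The Data analysis wording protects the second row. It does not protect the third, because it reaches only participants who are available.

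**2. What the mixed model can do.** Each participant has at most two walk tests: baseline and week 8. With the second missing, the model relies on the value being missing at random given little more than baseline and arm. Loss after fainting, dizziness or marked desaturation makes that assumption doubtful.

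**3. The plan's own figures** (Sample size and power calculations; Randomisation; Data analysis). Inputs: 50 recruited 1:1, 10% dropout, effect size 1.01, two-sided alpha 0.05, stated power 0.91.
- Completers: 50 × 0.9 = 45, as stated.
- Two-sample t-test, 22 against 23: noncentrality = 1.01 × √(22 × 23 / 45) = 3.39, power 0.9115. The stated 0.91 is reproduced.
- If all 5 allowed dropouts fell in the exercise arm (20 against 25): noncentrality = 1.01 × √(20 × 25 / 45) = 3.37, power 0.908.

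Power is therefore not the issue. Bias is.

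**4. Size of a possible bias (assumption).** The article gives no adverse-event or withdrawal rate. Suppose k of 25 exercise participants are lost and their change is 1 SD worse than that of the rest. The mean of those observed then exceeds the mean of all 25 by (k/25) × 1 SD:
- k = 2: 2/25 = 0.08 SD, and 0.08/1.01 = 7.9% of the planning effect.
- k = 3: 3/25 = 0.12 SD, and 0.12/1.01 = 11.9%.

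**5. Sensitivity to the assumption.** Simulation of 100,000 trials, 25 per arm, no true effect, k lost from the exercise arm only, t-test on the standardised change in those observed (a simple stand-in for the mixed model). Cells show bias in SD, then two-sided type I error. The correlation is between the reason for withdrawal and the change in walking distance. With no loss, type I error was 0.049.

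| Lost | Correlation 0.3 | Correlation 0.5 | Exactly the worst responders |
|---|---|---|---|
| 2 | 0.046; 0.054 | 0.076; 0.060 | 0.153; 0.094 |
| 3 | 0.064; 0.056 | 0.108; 0.068 | 0.217; 0.135 |
| 5 | 0.100; 0.063 | 0.168; 0.089 | 0.337; 0.238 |

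The last column is an upper bound.

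**The case against.** The best defence is that the article orders an evaluation. It does not order withdrawal, removal from the analysis set or an end to measurement. The study may simply be loose wording for the training programme. The physician may also properly be judging fitness for the study's own exercise tests, since week 8 includes a cycle cardiopulmonary test and imaging during exercise. Detailed retention rules may sit in the full protocol. All of this stands, and it limits the point to what the wording permits.

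Four stronger readings are tempting, and the documents do not support them:

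- **That the rule contradicts intention-to-treat.** It does not. Participants who stop the intervention are expressly kept, and someone withdrawn before week 8 is missing data within that approach.
- **That the worst responders are removed.** The article ties the review to adverse events and not to walking distance. A link is plausible but inferred.
- **That harm goes uncounted.** The triggering events are themselves a recorded outcome, and such events are recorded in both arms.
- **That 2-year follow-up is lost.** Clinical worsening is assessed at routine clinic visits every 3 to 6 months, and nothing says that stopping training ends this.

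The numbers are also open to challenge. The 10% dropout covers all causes in both arms, about 2.5 participants per arm if evenly split. The illustration gives the exercise arm's whole share to adverse-event withdrawal and assumes no offsetting loss among controls.

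**Conclusion.** The point holds as an ambiguity in trial conduct with a possible bias, and not as a contradiction. As written, the rule permits week-8 outcomes to be lost from the exercise arm alone, for reasons probably related to tolerance of exercise. Calling the mixed model ideal for dropouts is too strong with a single post-baseline walk test.

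The size is assumed throughout. With 2 to 3 of 25 lost and 1 SD worse than the rest, the inflation is about 0.08 to 0.12 SD. At a correlation of 0.3 it falls to about 0.05 to 0.06 SD, with type I error of 0.054 to 0.056. A reader might take the 0.24 type I error as the expected consequence, but it requires that exactly the five worst responders are lost, which nothing in the article suggests. Against a planning effect of 1.01 the plausible bias is modest. It is still worth correcting, because the remedy is cheap and the lost data could not be recovered.

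**What to change.** Reconcile the Intervention group and Data analysis sections:

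1. Name discontinuation of training and withdrawal from the study as two separate events, and record the reason and date of each.
2. State for both arms that neither an adverse event nor stopping training ends outcome follow-up. Unless consent is withdrawn, participants have the week-8 assessments that the physician judges suitable and are followed for 2-year clinical worsening.
3. Describe the mixed model as valid under missing at random, and drop the claim that it is ideal for dropouts.
4. Optionally, add one sensitivity analysis that assigns poor outcomes to week-8 values missing because of an adverse event, worsening or death.

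The rule for stopping training and the physician's clinical safety review are left unchanged. The cost is protocol wording, a few extra follow-up assessments and minor analysis work. The sample size does not change.

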### Control group

The control group participants will continue with their routine medical care and physical activity regimes for the 8-week study period without the additional exercise training intervention. During the 8-week period, participants allocated to the control group will receive a weekly phone call from the study coordinator to review any adverse events and to record exercise habits.

### Outcome measures

Baseline participant information including age, gender, anthropometrics (height and weight), co-morbid conditions and concomitant medications will be collected at the initial visit. In addition, various outcome measures will be undertaken at baseline, during and at completion of the 8-week study period. Clinical worsening will also be monitored for a minimum of 2 year period following commencement of the study (see below). All outcome measurements will be performed by a researcher blinded to the participants’ group allocation.

#### Primary outcome measure

The primary outcome measure will be exercise capacity assessed using the 6MWT at baseline and following the 8-week study period as per the American Thoracic Society and European Respiratory Society guidelines [22].

#### Secondary outcome measures

Cardiopulmonary exercise test is used to determine exercise capacity on a stationary cycle ergometer using previously described methods [23] before and after the 8-week study period. During the test, the participant will breathe through a mask so that oxygen uptake can be measured, using open circuit spirometry (Metamax, Cortex BXB, Lepzig, Germany) [24]. The metabolic system will be calibrated for volume and expired concentrations of oxygen and carbon dioxide prior to each test. Blood pressure, SpO_2_, HR and heart rhythm will be constantly monitored and the test will be supervised as per the ACSM guidelines [20]. All participants will commence cycling at 0 W for a 1 min period. The external workload will then be increased using a ramped protocol (5–10 W per minute, depending on disease severity and baseline exercise capacity), such that each test will be 8–12 min duration. At the completion of the test, participants will perform a supervised warm down. Peak minute average values for oxygen uptake ($$ \dot{\mathrm{V}}{\mathrm{O}}_2 $$), carbon dioxide production ($$ \dot{\mathrm{V}}{\mathrm{CO}}_2 $$), ventilation ($$ {\dot{\mathrm{V}}}_{\mathrm{E}} $$) and HR will be determined. In addition, breathing efficiency ($$ {\dot{\mathrm{V}}}_{\mathrm{E}}/\dot{\mathrm{V}}{\mathrm{CO}}_2 $$), end-tidal CO_2_ (P_ET_CO_2_), and anaerobic threshold will be determined using previously described methods [25]. The same ramped protocol will be used both pre- and post-exercise training.

Health-related QoL will be measured using a disease-specific PH tool, the Cambridge Pulmonary Hypertension Outcome Review (CAMPHOR) [26, 27] and the 36 item short-form survey (22). Health-related QoL will be assessed at baseline and following the 8-week study period.

Cardiac function will be measured using both cardiac magnetic resonance imaging (CMRI) and echocardiography, with CMRI serving as the principal method. Left and right ventricular end-diastolic volume and end-systolic volume will be measured using CMRI (1.5 T Scanner, MAGNETOM Aera, Siemens Healthcare, Erlangen, Germany) from which stroke volume, ejection fraction, cardiac output and contractile reserve will be derived [28]. In addition, measures of both right and left ventricular mass will be obtained. These will be measured at rest and during 2 submaximal exercise intensities (at 30% and 60% of their respective peak workload determined from incremental exercise test) using the MRI cycle ergometer. During the CMRI, electrocardiogram (ECG) and SpO_2_ will be continuously monitored and the test will be supervised by a medical practitioner. Echocardiographic evaluation will be performed as part of standard clinical protocol on the same day of the 6MWT. This will be assessed both at baseline and following the 8-week study period. Echocardiographic images will be acquired using a 4 MHz matrix array cardiac transducer (Vivid 7, General Electric, Milwaukee, Wisconsin, USA). All images will be attained with the participant in a semi-recumbent position for both the apical and parasternal windows. Right ventricular systolic pressure will be estimated from the tricuspid regurgitation velocity as per standard guidelines [29]. Right ventricular systolic function will also be examined by assessing the tricuspid annular plane systolic excursion.

Adverse responses or events including syncope, dizziness or marked worsening in oxygen desaturation during exercise will be monitored and recorded for the duration of the 8-week exercise training period. Such adverse events will also be assessed with weekly phone calls and recorded for the participants in the control group during the 8-week study period.

Long term outcomes will be analysed by examining survival and time to clinical worsening during routine follow-up clinic visits for a 2-year period following the participant’s commencement of the study. We will base this measure on the recent PH intervention studies [30–32]. For the purpose of this study clinical worsening will be defined as [30]:PH-related death orlisting for/completed lung transplantation orhospitalization for PH or clinical worsening leading to initiation of new PH-specific treatment orWorld Health Organisation (WHO) functional classification deterioration and a > 15% decrease in 6MWT from baseline.

Participants will be assessed for clinical worsening every 3–6 months following randomisation during routine clinical visits. A panel of two clinical experts, blinded to group allocation, will independently evaluate each participant for clinical worsening. Decisions will be moderated by a third expert, blinded to group allocation, in the event that the panel members reach a different decision.

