**Discussion:**

This study will determine whether an 8-week outpatient based supervised exercise training program is safe and beneficial for medically stable PH patients in the short and long term. This will be the first study to examine the impact of exercise training on right heart function using exercise CMRI. Results from the study will contribute new knowledge in relation to the impact of exercise training on cardiac function, long-term prognosis and inform clinical practice guidelines for this patient population. Moreover, the study will add to our understanding regarding the efficacy of exercise training in individuals with PH in an outpatient setting.

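### Exercise-related adverse events are recorded only to week 8, although home exercise follows and the abstract promises a long-term safety answer

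*Protocol article*

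**What the plan says.** All references are to the protocol article.

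- **Recording window, exercise arm** (Secondary outcome measures): syncope, dizziness and marked desaturation "will be monitored and recorded for the duration of the 8-week exercise training period".
- **Recording window, control arm** (same section): such events are asked about in weekly phone calls and "recorded for the participants in the control group during the 8-week study period".
- **Supervised exposure** (Intervention group): the exercise arm "will participate in an 8-week, twice weekly outpatient supervised exercise training program".
- **What follows** (Intervention group): "Following the exercise training program, participants will be prescribed a standard home exercise training program". This consists of the "participant being asked to walk 3–5 times per week for 20–30 min", at an exertion rating like that reached in training. No end date and no supervision are described.
- **What is checked during home exercise** (Intervention group): "Compliance with the home exercise program will be evaluated at subsequent clinic visits".
- **The promised conclusion** (abstract, Discussion): the study will determine whether the 8-week supervised programme is "safe and beneficial for medically stable PH patients in the short and long term".
- **What continues after week 8** (Secondary outcome measures): survival and clinical worsening for 2 years, assessed every 3 to 6 months in both arms, with clinical worsening judged by blinded experts.
- **Power for those outcomes** (Sample size and power calculations): the article describes the study as underpowered for them and offers them as pilot data.

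**The concern.** The recording window closes just as the exercise arm passes from monitored sessions to exercise at home. In the supervised sessions, heart rate, oxygen saturation and exertion are watched. For the home programme the article describes only a review of compliance.

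The protocol itself treats these events as important. Recent syncope or light-headedness on exercise excludes a patient (Participants), and the same kind of event during training leads to discontinuation and referral (Intervention group). An identical event at home in month 4 has no stated route into the trial data unless it leads to something that counts as clinical worsening.

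At stake is a main conclusion. The Background gives concern about disease progression and serious adverse events as the reason exercise has been discouraged in PH. If the report says the programme is safe in the long term, readers will assume that exercise-related harm was looked for throughout. Under the stated plan it is looked for over 8 weeks only.

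**Working it through.** The article gives no figure for how much of the follow-up its adverse-event recording covers, so there is none to reproduce.

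**1. Which events are captured, and when**

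| Event | To week 8 | Week 8 to 24 months |
|---|---|---|
| Death | Yes | Yes, through survival |
| PH admission, new PH treatment, transplant listing, functional-class decline with 6MWT decline | Yes | Yes, through clinical worsening |
| Syncope or dizziness | Yes, both arms | Only if it leads to a clinical-worsening event |
| Marked desaturation on exercise | Yes, both arms | Only if it leads to a clinical-worsening event |
| Exercise-related injury | Not named, but the list of events is open-ended | No stated collection |
| Non-PH serious event other than death | Not named, but the list of events is open-ended | No stated collection |

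**2. Length of the gap in calendar time**

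Inputs: 2 years of follow-up, taken as 104 weeks; recording window of 8 weeks.

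- Weeks outside the window: 104 − 8 = 96.
- Share: 96/104 = 92.3%.

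This needs no assumption about how long home walking lasts.

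**3. The gap as a share of prescribed sessions (illustration only)**

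Inputs: supervised sessions S = 8 × 2 = 16; home sessions H = (total weeks − 8) × 3 to 5. Share outside the window = H/(H + S). The article does not say how long home walking lasts, so the total is varied as an assumption.

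| Assumed end of home walking | Home sessions | Share outside the window |
|---|---|---|
| Week 16 | 24 to 40 | 60.0% to 71.4% |
| Week 26 | 54 to 90 | 77.1% to 84.9% |
| Week 52 | 132 to 220 | 89.2% to 93.2% |
| Week 104 | 288 to 480 | 94.7% to 96.8% |

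Under each assumption most prescribed sessions fall outside the window, but the share runs from 60% to 97%. These are prescribed sessions. They measure neither sessions performed nor risk.

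**4. Can the long-term outcomes carry a safety conclusion?**

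The article states 30% power for clinical worsening with 45 participants and risks of 0.26 and 0.64. I do not rely on that figure. A plain two-proportion comparison of the same risks with 22 to 25 per group gives about 73% to 79%, so the 30% should be checked separately. The present point holds either way. Either figure is power to detect a large benefit (risk ratio 0.26/0.64 = 0.41), and a study planned on that basis has not been planned to rule out harm.

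**The case against.** The strongest case on the other side has five parts.

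- **Event capture does not stop at week 8.** A reader might infer from the 8-week window that nothing is recorded afterwards. The article does not support that. Survival and clinical worsening run for 2 years in both arms with blinded adjudication, and syncope leading to a PH admission or new PH treatment would count. This stands, and it limits the point to events outside those outcomes.
- **A figure of about 95% of sessions unobserved is not established.** A reader might reach it by assuming home walking continues for the full 2 years. The article never says so. This stands, and the calendar-time figure is the one to use.
- **The abstract's safety sentence is about the 8-week supervised programme, and the article uses long-term outcomes to mean survival and clinical worsening.** This is a fair reading. It stands in part. A long-term safety answer still needs observation after week 8, and by then the allocated package includes home walking, so the two cannot be separated.
- **The main Discussion might be read as repeating the claim.** It does not explicitly do so. Its aim of avoiding significant training-related adverse effects fits the 8-week window, so only the abstract sentence needs attention.
- **Serious-event reporting may be in the full protocol or the charter of the safety board, which reviews participant safety with no 8-week limit.** Neither document is shown, so general reporting procedures cannot be called absent. But the window for the named adverse responses is stated in the article, so it is not a detail lost in condensing. The board can review only what is collected.

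**Conclusion.** The point holds in a limited form. The article sets a recording window for exercise-related adverse events that is too short for the long-term safety conclusion in its abstract. For about 96 of 104 weeks, exercise-related events and non-PH serious events that fall outside survival and clinical worsening have no stated collection. The figure takes the 2-year follow-up as 104 weeks and relies on the article alone.

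It would be wrong to infer that there is no follow-up after week 8, or that a known percentage of exercise sessions goes unobserved. The primary outcome and the 8-week safety comparison are unaffected. The change should be made because the abstract treats safety as a main result and, as described, the data would support it only for the supervised period.

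**What to change.** Preferred: at the clinic visits already planned every 3 to 6 months, through 24 months, ask both arms the same standard questions about syncope, dizziness, exercise-related injury and all serious adverse events, and record the answers as trial data. Leave out desaturation, which cannot be obtained by questioning after home exercise.

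The cost is a short question set and a little more data entry at visits that already take place. The limitation is recall over 3 to 6 months by participants who know their allocation. Mild dizziness will be under-reported; syncope, injuries and admissions should be recalled better. The report should say so.

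Alternative, with no added data collection: limit the safety conclusion in the abstract to the 8-week supervised period, and describe the long-term data as survival and clinical worsening only.
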